## Discussion

This study protocol describes a randomized control trial testing a culturally adapted depression education intervention designed to reduce stigma and increase disease literacy. The target of the three-part design is to improve detection, diagnosis, and increasing uptake in depression treatment among Hispanics in an integrated care model in a community-based health center. This study addresses the need for both identification and elimination of the barriers to treatment for the most common mental health condition affecting Hispanics. Various other design options were discussed, including testing the *fotonovela* as a discrete intervention, without the context of integrated care. However, with the U.S. Preventive Services Task Force recommendation for universal screening for depression in primary care settings and the emphasis on systems to address positive screens [61], the rationale for testing an innovative technology to facilitate screening and implementing an evidence-based treatment model for which there is a lack of studies among minority populations offers a greater opportunity to translate established research into clinical practice. The rationale for designing a complete intervention, while still testing a specific element for which cultural values about mental health may be distinct, appears scientifically feasible, and shows scientific promise.

The strengths and weakness of using a SE control group were carefully considered prior to selection. The primary benefit of the SE control group is that it ensures a comparable contact across the two interventions. As a result, a significant effect observed in the *fotonovela* condition cannot be attributed to differences in contact or participation outcome expectations. A potential concern with the control group is a threat to internal validity due to lack of treatment fidelity and interventionist allegiance. To reduce these concerns, the SE intervention will be manualized (based on NIMH education materials) and intervention fidelity procedures will be the same across the two interventions.

The scope of this project is ambitious, in that we aim to change provider behavior and screen all adult primary care patients for depression. With that in mind, we realize that we will identify a large number of patients whose depression was previously unrecognized. For busy primary care practitioners, this will undoubtedly increase their workload. However, with the support of the DCM and MBIC, the burden of systematic measurement, education about the disease and tracking of outcomes will be reduced. Additionally, we look to offset the potential treatment burden by training the PCPs and their clinic staff in evidence-based treatment guidelines, and through the use of the iPad Depression Screening and Monitoring application. It is anticipated that the recognition and treatment of depression will improve other co-morbid chronic disease and ultimately reduce the overall burden of disease management on the primary care practice.

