### Aims and objectives

The study aims to examine a novel culturally adapted patient education intervention to increase engagement by Hispanics in depression treatment. The intervention will be implemented after diagnosis using an innovative screening technology and via measurement-based integrated care for the treatment of depression, which will have a substantive impact on reducing mental health disparities in the Hispanic population.

#### Specific aim 1

Examine the specific effects of a Depression Education *Fotonovela* (DEF) to increase knowledge of depression, reduce stigma, and increase engagement in depression treatment among Hispanic patients.

#### Specific aim 2

Evaluate the impact of measurement-based integrated care (MBIC) on retention in treatment and remission of depression symptoms in one community-based Federally Qualified Health Center (FQHC) in North Texas whose patient population is majority Hispanic.

#### Specific aim 3

Examine the feasibility of universal screening and accurate detection of depression among adult primary care patients utilizing innovative iPad Depression Screening technology.

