#### Education

Within one week, patients will return to the clinic to complete their education session and study measures with a research assistant – either SE or DEF, depending on the group to which the patient was randomized. Two bilingual research assistants, hired from the school of social work, will be assigned and trained to deliver the different education interventions (one each, without exposure to the other education materials). Patients will be encouraged to bring family members or loved ones to the education session. Each education session will be provided in English or Spanish, depending on patient preference, and will conclude with compensation to the patient upon completion of the study measures.

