##### Standard education

The research assistant trained in SE will read the patient education materials from the National Institute of Mental Health (NIMH) [42] which includes: What is depression? What causes depression? Signs and symptoms. Who is at risk? Treating and living with depression. The SE materials emphasize the complexity of depression that involves thoughts and feelings, behaviors, and physical symptoms, and issues of co-morbid illness and depression as a biological disease. The SE education materials are printed in English and Spanish. The SE session will last about 20 min.

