##### Depression education fotonovela

The research assistant trained in the DEF will read *Secret Feelings* (*Sentimientos Secretos*) with the patient, including the question and answer page at the back of the booklet. The story is presented in both English and Spanish at a 4th-grade reading level. After reading the *fotonovela* together, the patients will be asked if they have any additional questions. The DEF session will last for about 30–45 min.

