##### Intervention fidelity and data monitoring

Each research team member will undergo depression education training with the Principal Investigator and protocol and data collection training with the Project Coordinator. Research assistants will meet with the Principal Investigator and perform a final, practice education session prior to depression education intervention visits with participants. Additionally, education sessions will be audio recorded (with patients’ consent) and regularly reviewed by the Principal Investigator to assure adherence to the protocol. The Project Coordinator will perform data audits quarterly to assure data collection accuracy.

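### The Discussion rules out contact as an explanation of a fotonovela effect, but the fotonovela session is planned to last 1.5 to 2.25 times as long as the control session

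*Protocol article*

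**What the plan says.** The Discussion of the protocol article defends the choice of control: "The primary benefit of the SE control group is that it ensures a comparable contact across the two interventions". The next sentence draws the inference that a significant effect in the fotonovela "condition cannot be attributed to differences in contact or participation outcome expectations".

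The Education subsections give the planned session lengths:

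- Standard education: "The SE session will last about 20 min".
- Depression education fotonovela: "The DEF session will last for about 30–45 min". This session includes the booklet's question-and-answer page, and afterwards "the patients will be asked if they have any additional questions".

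Specific aim 1 begins "Examine the specific effects of a Depression Education" and names the fotonovela as the object. Under Education, patients return to "complete their education session and study measures with a research assistant", so the first outcome measurement after randomization belongs to the same visit as the education.

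On the secondary matter, the Randomization section places the randomization list in a locked cabinet in the office of the depression care manager (DCM), has the DCM book the education visit, and has the Project Coordinator keep a log of assignments. The Intervention and Measurement-based integrated care (MBIC) sections give MBIC to every patient, with DCM visits every 1–4 weeks.

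**The concern.** An attention-matched control lets a trial separate what an intervention contains from the time spent delivering it. The Discussion claims that property and calls it the main benefit of the SE arm. If the contact is not matched in time, a better knowledge or stigma score after DEF could come from the fotonovela's content and format, from more minutes one-to-one with a research assistant, or from both. The design cannot tell these apart.

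This bears mainly on Aim 1. The Depression Knowledge Measure and the three stigma scales are taken after the education session, directly following the unequal contact, and the first MBIC appointment comes later. If the sentence stands, the claim that contact has been excluded can pass unchanged into the results paper.

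A second, weaker matter is who can learn the arm. The DCM enrolls patients, takes baseline measures, books a visit with one of two assistants who each deliver a single type of education, and then treats both arms at a pace that depends on the treatment plan. A DCM who knew the arm could, in principle, pursue treatment more actively in one arm, which would touch treatment engagement and the 12-month PHQ-9.

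**Working it through.** The article gives no figure for contact time beyond the session lengths, so there is no stated result to reproduce. The check compares the lengths with the claim.

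**Inputs**

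| Item | SE | DEF | Section |
|---|---|---|---|
| Education sessions per patient | 1 | 1 | Education |
| Planned length | about 20 min | about 30–45 min | Standard education; Depression education fotonovela |
| Delivered by | one bilingual research assistant, SE only | one bilingual research assistant, DEF only | Education |
| Later care | MBIC | MBIC | Intervention |

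**Step 1, difference per patient** (DEF minus SE)

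- Lower end: 30 − 20 = 10 min
- Upper end: 45 − 20 = 25 min

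**Step 2, ratio** (DEF divided by SE)

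- Lower end: 30 / 20 = 1.5
- Upper end: 45 / 20 = 2.25

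**Step 3, does anything restore the balance?** Visit count, setting, language choice and follow-up visits are common to both arms. No section adds time or an attention component to SE. The safeguards named in the Discussion, a manualized SE and identical fidelity procedures, address adherence and interventionist allegiance. Faithful delivery of both manuals keeps the 10–25 min gap rather than closing it.

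**Step 4, what follows.** Contact is comparable in number and format of sessions but not in planned time. The sentence excluding differences in contact needs both. The effect of 10–25 extra minutes on knowledge or stigma scores cannot be derived from the article, and no figure is offered.

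**DCM point.** No arithmetic is needed. Read together, the list's location, the booking of an assistant tied to one arm, and the later treatment of all patients show that the DCM could easily learn the arm. They do not show that the DCM does, or acts on it. Knowledge and stigma scores taken at the education visit precede MBIC, so they lie outside this route.

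**The case against.** The best defense is that *comparable* does not mean *equal*. Both arms get one session at the same clinic with a bilingual assistant, in the preferred language, with family welcome and the same compensation for completing measures. The lengths are printed openly, Aim 1 is already analyzed as MBIC + DEF against MBIC + SE, and no test or sample size rests on the Discussion sentence.

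Much of this stands. The first sentence is partly true, and the fault lies mostly in the inference that follows it. Equal visit count cannot rule out contact as an explanation when one session may run to more than twice the length of the other.

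A reader might infer more than the article supports:

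- *That the randomized comparison is biased.* It is not. Longer contact is part of what DEF patients are assigned to, and the contrast is valid for that package.
- *That SE patients may not ask questions.* The SE section describes reading only, but a condensed article's silence is not evidence of a difference. The point rests on length alone.
- *That the claim about outcome expectations is also wrong.* It sits in the same sentence, but nothing in the session lengths refutes it.
- *That the DCM is unmasked and favors an arm.* The article neither claims masking nor says that the DCM consults the list. The cabinet is locked and key access is not stated. The PHQ-9 is self-reported on an iPad, symptoms are measured at defined intervals, and treatment plans are made with the primary care provider. These limit the route without closing it.

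**Conclusion.** The claim that differences in contact are excluded is wrong as written. Planned education contact is 10–25 min longer in DEF, 1.5 to 2.25 times the SE length, and nothing in the article offsets this. Confidence is high. It assumes only that the sessions run roughly as planned; both lengths are approximate, and actual times could lie closer together or further apart.

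The consequence is confined to attribution. Aim 1 can estimate the effect of the DEF session as delivered, but not the effect of fotonovela content net of time. This should be corrected, and it does not threaten the trial's validity.

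The DCM matter is a precaution held with lower confidence. Access to the arm is a reasonable inference from the procedures; knowledge of it, and any resulting bias, are not shown, and neither size nor direction can be given.

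**What to change.** **Main change.**

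1. In the Discussion, limit the claim to number and format of sessions, for example: *Both groups receive one education session of the same format. The DEF session is planned to be longer (about 30–45 min against about 20 min), so contact time remains a possible explanation of an effect.* Leave the statement on outcome expectations in place unless it is separately shown to be wrong.
2. Interpret Aim 1 as the effect of the DEF session as delivered.
3. Report actual session length by arm. The Intervention fidelity section already plans that "education sessions will be audio recorded" with consent; where a patient declines, the assistant logs the length. Use it descriptively: length is tied to the arm, so adjusting for it would not reliably separate time from content.

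The cost is a few sentences and one table. Lengths will be incomplete for past sessions that were not recorded. Lengthening SE to match is not proposed, because it would alter the control arm after enrollment began in February 2016.

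**Precaution for remaining patients.** The Project Coordinator, who already keeps the assignment log, holds the list and books the education visit without passing the arm to the DCM. Report MBIC sessions by arm. This moves one list and one booking task to existing staff and adds one count. Masking would be partial, since some patients will reveal their arm, and patients already enrolled gain only from the reporting. The MBIC schedule does not change.

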### Trial status

Enrollment for METRIC commenced in February 2016. The estimated completion date of enrollment is January 2018, with 12-month follow-up and data lock by January 2019.

## Abbreviations

BA: Behavioral activation
DCM: Depression care manager
DEF: Depression education *fotonovela*
DKM: Depression Knowledge Measure
EHR: Electronic health record
FQHC: Federally qualified health center
GAD-7: Generalized Anxiety Disorder-7
HHS: U.S. Department of Health and Human Services
LCSW: Licensed clinical social worker
LEP: Limited English proficiency
LSAS: Latino Scale for Antidepressant Stigma
MBIC + DEF: Measurement-based integrated care with depression education *fotonovela*
MBIC + SE: Measurement-based integrated care with standard education
MBIC: Measurement-based integrated care
METRIC: Measurement, Education, and Tracking in Integrated Care
NIMH: National Institute of Mental Health
PAQ: Patient Adherence Questionnaire
PCP: Primary care provider
PHQ-9: 9-item Patient Health Questionnaire
PI: Principal Investigator
PST-PC: Problem Solving Treatment for Primary Care
SCMHC: Stigma concerns about mental health care
SD: Social Distance Scale
SE: Standard education
